### Ethical issues

2.17

The trial research protocol adheres to the principles of the Declaration of Helsinki and has been approved by the Ethics Committee of Shanghai Putuo District Central Hospital (PTEC-A-2024-46-2). In the case of any changes to the study protocol, researcher will promptly report the modifications to the Ethics Committee. Before the study begins, researcher will undergo informed consent training and draft an informed consent form to ensure that participants are fully informed about the study process.

## Discussion

3

Since ischemic stroke poses a severe threat to health, thrombolysis and thrombectomy after acute stroke can effectively reduce stroke-related mortality and disability rates (30). However, the strict time window for these treatments limits stroke patients’ therapeutic benefits (31). Most patients experience varying degrees of neurological deficits after acute stroke, with approximately 50–80% developing limb motor dysfunction related to ischemic lesion during recovery period, which indicates a significant demand for post-stroke functional rehabilitation (32). The Stroke Roundtable Consortium defines the first 24 h post-stroke as the hyperacute phase, the first 7 days as the acute phase, the first 3 months as the early sub-acute phase, 4–6 months as the late sub-acute phase, and beyond 6 months as the chronic phase (33). In the early post-stroke period, a series of neuronal plasticity-enhanced mechanisms trigger dendritic growth, axon sprouting, and the formation of new synapses (34). The “proportional recovery rule” suggests that patients can recover approximately 70% of lost function within 3–6 months post stroke (35), though this proportion varies with individual differences, lesion location and severity, as well as the effectiveness of rehabilitation measures. Therefore, seizing the critical time window for post-stroke rehabilitation and implementing effective rehabilitation measures are crucial for restoring impaired neural functions, improving disease prognosis, and enhancing patients’ quality of life.

In TCM, phlegm turbidity and blood stasis are considered two major pathogenic factors contributing to ischemic stroke, persisting throughout the entire course of the disease (36). Therefore, guided by TCM theory and prior treatment experience, this study primarily selected acupoints on the Hand and Foot Yangming Meridians and the Foot Taiyin Spleen Meridian for acupuncture treatment, aiming to tonify qi, activate blood circulation, resolve phlegm, and dredge the meridians. Additionally, Waiguan on the Hand Shaoyang Sanjiao Meridian is selected to regulate qi movement and unblock the meridians, while Xuanzhong on the Foot Shaoyang Gallbladder Meridian is chosen to strengthen tendons and bones, and nourish the brain and marrow. The selection and combination of these acupoints align with the pathogenesis characteristics of stroke, reflecting the differentiation and treatment feature of “simultaneous treatment of phlegm and blood stasis.” Currently, there are few reports on RCTs that evaluate the therapeutic efficacy of acupuncture for ischemic stroke using both subjective and objective indicators, aiming to assess the syndrome differentiation-based acupoint selection in TCM, and to explore its underlying mechanisms. Herein, guided by the SPIRIT principle, we designed a single-center, randomized, assessor-and-statistician-blinded, sham acupuncture-controlled clinical trial to evaluate the efficacy of the “simultaneous treatment of phlegm and blood stasis” acupuncture therapy in improving limb motor function in ischemic stroke patients with hemiplegia. We used functional assessment scales combined with EEG to evaluate the efficacy, and explored its potential electrophysiological mechanisms by recording EEG activity. In this study, we have set the intervention time for acupuncture treatment to be between 1 week and 3 months post-stroke. After the 7-day acute phase, stroke enters the recovery phase, during which patients’ physical conditions stabilize, vital signs remain relatively steady, enabling them to tolerate and adapt to various rehabilitation treatments. Based on neurorehabilitation theory, active rehabilitation within 3 months post-stroke, defined as early recovery, is more conducive to propelling patients into the fast lane of functional recovery. And we will administer 10 acupuncture sessions (5 consecutive days per week for 2 weeks) to stroke patients with limb dysfunction during the early recovery phase, aiming to capture the optimal window for post-stroke rehabilitation. Clinical observation indicates that 10 sessions of acupuncture can lead to a certain degree of improvement in limb motor function (11). Moreover, an appropriate treatment course enhances patients’ compliance and cooperation. Given varying degrees of disease severity, some patients may choose to continue rehabilitation after the 2-week treatment. Thus, we did not schedule a follow-up assessment after the end of the treatment course. Furthermore, ischemic and hemorrhagic strokes exhibit distinct pathological mechanisms across all disease stages. Given these significant differences in disease progression, symptom manifestations, prognosis, and treatment responsiveness between the two stroke types, hemorrhagic stroke was excluded from the current study. Apart from that, since some neuromodulation techniques, such as transcranial magnetic stimulation (TMS), can modulate brain oscillatory activities to promote neuroplasticity (25), and these techniques have been found to achieve long-term effects on motor function recovery post stroke (37), patients who received TMS within one month were set as an exclusion criterion to avoid interference with EEG signals.

Outcome measures include the simplified Fugl-Meyer Assessment for motor function, the Berg Balance Scale, the Fugl-Meyer Assessment for sensory function, the Modified Ashworth Scale, the Modified Barthel Index, and TCM syndrome scoring scale, which are used to comprehensively evaluate the efficacy of the “simultaneous treatment of phlegm and blood stasis” acupuncture therapy based on syndrome differentiation on improving limb mobility, balance, sensation, muscle tone, activities of daily living, and TCM-related symptoms/signs in ischemic stroke patients with hemiplegia. Resting-state EEG is highly sensitive to cerebral metabolic and neurological functional abnormalities, serving as an important method for assessing post-stroke brain function (38). Commonly used frequency bands in EEG include alpha, beta, theta, and delta waves. Alpha wave activity during rest reflects the level of consciousness and visual attention (39). With a frequency range of 8–13 Hz, alpha waves are brain rhythms involved in various functions, ranging from sensorimotor processing to memory formation (40). Research indicates a linear relationship between reduced synchrony of alpha wave oscillations among brain regions and cognitive/motor function impairments in stroke patients (41). Beta waves, oscillating at 13–30 Hz, are crucial rhythms in cortical activity, closely related to motor control and sensorimotor integration (42), with their generation involving the synergistic action of pyramidal and inhibitory neurons (43). Research has found that beta wave coherence can serve as a marker for cortical functional plasticity after stroke (42). Delta waves are low-frequency waves with frequencies ranging from 1–4 Hz, and can be detected during slow-wave sleep and execution of cognitive tasks (44). Theta waves, with frequencies in the 4–8 Hz range, have been extensively studied in emotional and cognitive domains. Recent research has found that perturbation during seated movements can evoke differential theta-band responses in the anterior cingulate cortex and supplementary motor areas (45). In this study, we will employ EEG to record and analyze the frequency, amplitude, and spectral power of delta, theta, alpha, beta waves. We will designate the M1 region as the seed region and calculate the coherence of alpha and beta waves between the seed region and other regions. By observing changes in neuronal oscillation frequencies, electrical activity intensity, and functional connectivity across different brain regions before and after treatment, we aim to explore the neurophysiological mechanisms, by which acupuncture improve limb function in stroke patients, and screen EEG-based biomarkers with predictive value.

There are still some limitations in the design of this study: (1) the study does not restrict the infarction sites of included patients to the same hemisphere or specific locations, leading to increased heterogeneity in EEG signals; (2) the study duration is short, and there is a lack of follow-up observation after treatment course, making it difficult to ascertain the long-term efficacy of acupuncture therapy; (3) due to the treatment characteristics of acupuncture, it is challenging to implement blinding for acupuncturists and patients; (4) a multicenter study is not designed, making it impossible to verify the general applicability of the study across different populations and medical conditions. Hence, based on this study, we will further conduct multicenter, large-sample, long-term follow-up clinical trials for ischemic stroke patients in recovery stage.

Collectively, the primary objective of this clinical trial is to evaluate the efficacy and safety of the “simultaneous treatment of phlegm and blood stasis” acupuncture therapy in improving limb motor impairment in ischemic stroke patients with hemiplegia using functional scales, while exploring its underlying electrophysiological mechanisms through EEG. By conducting this clinical study, we expect to provide reliable scientific evidence for the clinical application of acupuncture therapy featuring characteristic acupoint combinations based on TCM syndrome differentiation in the field of neurological rehabilitation for ischemic stroke.

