Electroencephalogram (EEG) is an important method for assessing brain function and widely used in clinical practice. It tracks and records the tiny electrical signals produced by cortical neuronal activity in real time by placing electrodes on the scalp. Brainwaves in different frequency bands reflect synchronized neuronal activities across distinct brain regions (19). Since EEG has a temporal resolution in milliseconds, it can capture changes in neuronal electrical activity more rapidly than MRI and is highly sensitive to abnormalities in brain metabolism and neural function (20). Due to its simplicity and non-invasive nature, EEG has been applied to evaluate the therapeutic effect after intervention for brain diseases. As evidenced by EEG, in stroke patients with better clinical outcomes, the healthy hemisphere tended to compensate for the affected side, and kinematic and EEG metrics were reported to be relevant for evaluating early post-stroke motor recovery (21). Additionally, event-related desynchronization (ERD) during action observation, reflecting reduced coordination of neural activity, was validated as an early predictor of motor recovery in subcortical stroke (22). These metrics provide important prognostic information that can be used to optimize treatment strategies. Herein, we design a randomized, assessor-and-statistician-blinded, parallel-controlled clinical trial, for assessing the efficacy and safety of acupuncture therapy, featuring acupoint combination for “simultaneous treatment of phlegm and blood stasis,” in treating limb dysfunction in ischemic stroke patients with hemiplegia. We will employ functional scales to evaluate patients’ clinical outcomes and use EEG to capture neurophysiological changes after acupuncture, including neural excitability and brain functional connectivity. Further, EEG metrics will be linked with clinical outcomes, demonstrating its multiple values in efficacy assessment, mechanism interpretation, and prognosis prediction.

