### Study design

2.1

This is a single-center, assessor-and-statistician-blinded, randomized, sham acupuncture-controlled clinical trial. The study aims to evaluate the efficacy and safety of acupuncture therapy, featuring acupoint combination for “simultaneous treatment of phlegm and blood stasis,” in treating ischemic stroke patients with hemiplegia. The study has been registered on itmctr.ccebtcm.org.cn (Registration No. ITMCTR2025001171). SPIRIT checklist is shown in Supplementary file 1.

The study will recruit 70 eligible ischemic stroke patients with unilateral limb dysfunction who meet the inclusion criteria. After signing informed consent, the participants will be randomized into acupuncture group or sham acupuncture group in a 1:1 ratio. All participants will receive a two-week treatment. Basic information will be collected before treatment (Day −1 to 0), and electroencephalogram (EEG) examination and scale evaluation will be conducted before (Day −1 to 0) and after the two-week treatment (Day 15). Allocation information will be confidential to assessors. The study process is shown in Figure 1 and the timeline for enrolment, intervention and assessment is shown in Table 1. The study will be started in June 2025 and complete recruitment by June 2028. The entire study is expected to be finalized by December 2028.

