#### Primary outcome

2.12.1

The primary outcome is the change in limb motor function in stroke patients before and after treatment, assessed using the simplified Fugl-Meyer Assessment (FMA) scale. Limb motor function impairment will be quantified by evaluating upper/lower extremity functions, balance, sensation, and joint range of motion. The scale comprises 50 items (33 for upper limbs, 17 for lower limbs), with higher scores indicating better functional activity.

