### Statistical analysis

2.16

All data will be analyzed using SPSS 27.0 statistical software. In accordance with the intention-to-treat (ITT) principle, patients who have received at least one treatment session will be included in the analysis. Basic information, baseline data, and efficacy evaluation will be analyzed using both the full analysis set (FAS) and per-protocol set (PPS). In case of inconsistent results between the two datasets, further analysis and evaluation will be conducted. Missing data will be imputed using multiple imputation method. For continuous outcomes, post-treatment data are presented as mean±SD if normally distributed with equal variances; otherwise, they are presented as median (IQR). ANCOVA will be used to adjust for baseline values and confounders (e.g., age, gender, revascularization therapy status), with adjusted mean differences and 95% CIs reported. For categorical data, frequencies and percentages will be presented, and potential confounders will be screened via univariate analysis before constructing stepwise logistic regression models to adjust for confounders and report odds ratios with 95% CIs, followed by validation of the model’s goodness of fit. Further, patients will be grouped based on infarction location to analyze EEG indicators in each subgroup. Receiver operating characteristic (ROC) curve analysis will be conducted to evaluate the predictive value of EEG as an efficacy indicator for acupuncture response, with the area under the curve (AUC) and 95% CI reported. For correlation analysis, Pearson correlation will be applied to normally distributed continuous data, while Spearman correlation will be used for ordinal data. All data analysis will be conducted using two-tailed tests with a significant level of 5%.

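### The Discussion ties the screening of predictive EEG biomarkers to pre-to-post EEG change, which is complete only at the visit where the outcome is scored and so can show concurrent association, not prediction

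*Protocol article*

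**What the plan says.** **The marker and its purpose.** In the Discussion, the paragraph on outcome measures and EEG closes with a sentence that opens "By observing changes in neuronal oscillation frequencies, electrical activity intensity, and functional connectivity across different brain regions before and after treatment" and names two purposes: to explore mechanisms "and screen EEG-based biomarkers with predictive value". The Introduction says that EEG will capture changes after acupuncture and that EEG metrics will be linked with clinical outcomes, "demonstrating its multiple values in efficacy assessment, mechanism interpretation, and prognosis prediction". The Abstract repeats the aim of finding predictive biomarkers without saying which EEG quantity serves it.

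**The timing.** Section 2.1 and Table 1 put EEG and every clinical scale at the same two times, before treatment (Day −1 to 0) and Day 15. Section 2.12.1 defines the endpoint over that interval: "The primary outcome is the change in limb motor function in stroke patients before and after treatment". On anything later, the Discussion says: "Thus, we did not schedule a follow-up assessment after the end of the treatment course".

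**The analysis.** Section 2.16 states: "Receiver operating characteristic (ROC) curve analysis will be conducted to evaluate the predictive value of EEG as an efficacy indicator for acupuncture response". It does not say whether the EEG variable is the baseline value, the Day 15 value or the change.

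**The concern.** A predictive or prognostic marker has to be known before the outcome that it forecasts. The only sentence that says which EEG quantity will serve the biomarker aim names the change over treatment. That change cannot be computed until Day 15, when the FMA outcome is scored, and nothing is measured afterwards against which it could be tested.

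At stake is what an exploratory result would be taken to mean. If the analysis follows the Discussion sentence, an association between two changes over the same two weeks would be reported as prediction. A reader could then believe that EEG forecasts recovery, or response to acupuncture, when the data show only that the two moved together. This is a matter of time order, so it does not depend on which arm is analysed or on how the AUC is validated.

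**Working it through.** The point rests on no figure in the plan, so there is none to reproduce. The check sets the passages side by side and then adds one illustration.

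**Step 1: when each quantity is known** (section 2.1, Table 1, section 2.12.1)

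| Quantity | Recordings needed | Known at | Lead over the Day 15 FMA score |
|---|---|---|---|
| Baseline EEG | Day −1 to 0 | Day −1 to 0 | about two weeks |
| Day 15 EEG | Day 15 | Day 15 | none |
| EEG change | Day −1 to 0 and Day 15 | Day 15 | none |
| FMA change | Day −1 to 0 and Day 15 | Day 15 | (the outcome) |

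**Step 2: is there a later outcome?** The Discussion says that none is scheduled, so Day 15 EEG and EEG change precede no measured outcome.

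**Step 3: which row does the plan use for prediction?** The Discussion sentence points to the third row. The Abstract and section 2.16 name no row. Baseline EEG is collected and could support short-term prediction of the Day 15 outcome, but no predictive or prognostic statement is limited to it.

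**Step 4: illustration on assumed values.** Suppose that EEG change X and FMA change Y are jointly normal with correlation r, and that response means an above-median Y. The documents give neither r nor a definition of response. Under these assumptions

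AUC = 1/2 + (2/π) · arcsin(r/√2).

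- r = 0.2: 0.5 + 0.6366 × 0.1419 = 0.590
- r = 0.3: 0.5 + 0.6366 × 0.2138 = 0.636
- r = 0.4: 0.5 + 0.6366 × 0.2868 = 0.683
- r = 0.5: 0.5 + 0.6366 × 0.3614 = 0.730

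Simulation with 400,000 pairs gives 0.590, 0.636, 0.683 and 0.732, which agrees to within simulation error. A baseline EEG generated independently of the outcome has an AUC of 0.50 throughout. An AUC in this range can therefore arise from concurrent association when no forecasting information exists. The figures only put the assumed r on the AUC scale and say nothing about the size of any association in this trial.

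**The case against.** **The plan may not commit to this analysis.** The tie to EEG change rests on one Discussion sentence in which a single opening phrase covers two aims. The Abstract and section 2.16 name no time point. The Introduction cites an early EEG predictor of motor recovery, which fits a baseline marker. This stands in part. A reader might infer that the trial cannot study prediction at all, or that the ROC will certainly be run on EEG change. The documents support neither, because baseline EEG is collected before the outcome and section 2.16 leaves it open.

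**The time point of an exploratory ROC is normally left to an analysis plan that is not shown.** Silence in section 2.16 alone would be no finding. Here, however, the article states a means that cannot deliver the stated aim, and that is wrong whatever a fuller document adds.

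**The ROC sentence has a legitimate concurrent reading.** It concerns EEG as an indicator of efficacy, and the Introduction lists efficacy assessment first among the uses of EEG. Asking whether EEG change separates responders from non-responders at Day 15 is a valid use of ROC. This stands in full: the objection is to the predictive label, not to the analysis.

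**The harm can be overstated.** A reader might infer that patients would be selected for acupuncture on EEG change, or that shared same-day noise drives the association. No passage proposes such selection. The EEG data collection section asks patients to avoid caffeine, sedatives, stimulants, fatigue and hunger and to sleep adequately before recording, which reduces the obvious sources of same-day noise without removing them.

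**The limitations already mention the missing follow-up.** They do, but only as a limit on judging long-term efficacy and not on the biomarker aim.

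**Conclusion.** The concern holds for EEG change and Day 15 EEG. Both are complete only when the outcome is scored, with no later outcome, so they can support a statement of concurrent association with FMA change and nothing about prediction or prognosis. It does not hold for baseline EEG, which precedes the Day 15 outcome.

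The conclusion rests on the visit schedule and on reading the Discussion sentence as written; no numerical assumption is needed. The AUCs of 0.59 to 0.73 are illustrations that depend on assumed correlations, joint normality and a median split. The matter concerns the labelling and definition of an exploratory aim. The primary efficacy comparison is untouched, but the wording should be corrected before the EEG data are analysed.

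**What to change.** In section 2.16, and wherever the biomarker aim appears (Abstract, Introduction, Discussion):

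1. Define every analysis called predictive or prognostic, including any ROC so described, as using EEG from Day −1 to 0 to predict Day 15 FMA, adjusted for baseline FMA.
2. Keep EEG change and Day 15 EEG, analysed by correlation or ROC if wanted, but label them concurrent indicators of response and drop the predictive wording for them.
3. Reword the Discussion sentence so that observing change serves the mechanistic aim and baseline EEG serves the predictive one.

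This needs no new data or visits and can be done while the trial is recruiting. The cost is that the AUC for baseline EEG may be less favourable than one for EEG change.

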## Trial status

4

This trial is now recruiting participants.
